### Co-interventions

Participants will indicate whether they have taken common arthritis medications over the past month for their study hip at baseline. At 6 and 12 months, participants will indicate whether they used oral opioid medication, paracetamol or paracetamol combinations and oral anti-inflammatories for their study hip ‘less often’, ‘more often’ or the ‘same as before’ (over the past month). At baseline, 6 and 12 months, participants will complete a customised questionnaire regarding prescription and non-prescription medications including injections, over the past 6 months.

### Sample size calculation

We aim to detect a MCID between groups of 1.8 NRS units in change in overall hip pain severity (baseline minus 6 months) [36]. We have performed the sample size calculation taking into account differential clustering between arms. As the physiotherapists treat participants in both arms of the trial, only the clustering by dietitians was accounted for in the sample size calculation. We have assumed a conservative standard deviation at baseline across all participants of 2.5 units and a conservative correlation between baseline and 6-month scores of 0.25, as guided by our other research [44]. We have also assumed an intra-cluster correlation of 0.05 and that there will be 5 dietitians treating approximately 8 patients each. Given these parameters, we need 40 per arm to achieve 80% power to detect the MCID in pain at a 0.05 significance level. Allowing for 20% attrition, we will recruit 50 people per arm in total (*n* = 100).

### Statistical analyses

A biostatistician will analyse blinded data. Main comparative analyses between groups will be performed using intention-to-treat. Multiple imputation will be used if the primary outcome has greater than 5% missing data. For the primary hypothesis, differences in mean change in pain (baseline minus follow-up) will be compared between groups using a mixed-effects linear regression model including all data from 6 and 12 months for each participant with random effects for participants, and accounting for clustering by physiotherapist and dietitian as appropriate. The model will be adjusted for baseline values and the stratifying variables of site (Sydney/Melbourne) and sex. Similar mixed-effects linear regression models will be used for continuous secondary outcomes measured at baseline, 6 months, and 12 months. The proportion of participants in each group that show an improvement that reaches or exceeds the MCID in pain (≥1.8 units) will also be calculated. For this and other binary outcomes, groups will be compared using risk differences and risk ratios, calculated from logistic regression models adjusted for the stratifying variables of site location and sex, and fit using generalized estimating equations to account for clustering. All effect sizes, 95% confidence intervals and *p*-values will be reported and used to interpret the results. Standard diagnostic plots will be used to check model assumptions. A full statistical analysis plan, including a description of secondary analyses (e.g. mediation analyses and/or health economic analysis) will be published prior to undertaking the formal analysis of collected data.

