**Harms**		
Adverse events		6 and 12 months

Secondary outcomesi)Body weight, measured in kilograms. Participants will be asked to use the same set of scales across the time-points;ii)Body mass index, measured in kg/m^2^;iii)Visceral fat mass, measured in grams and percentage of total body mass;iv)Total body fat mass, measured in grams and percentage of total body mass;v)Hip pain, measured as the proportion who meet or exceed the minimal clinical important difference (MCID) in NRS pain (at least 1.8 units of improvement) [36];vi)Hip Osteoarthritis Outcome Scale (HOOS) pain subscale, normalised to 0–100 scale (100 indicating no symptoms and 0 indication extreme symptoms) [37];vii)HOOS activities of daily living subscale, normalised to 0–100 scale (100 indicating no difficulty and 0 indication extreme difficulty) [37];viii)HOOS quality of life subscale, normalised to 0–100 scale (100 indicating better quality of life and 0 indication lower quality of life) [37];ix)Health-related quality of life, measured using the Assessment of Quality of Life Instrument (AQoL-8D) [38];x)Global rating of change in physical activity, scored on a 7-point Likert scale for “change in your physical activity levels since you began the study” from “much less” to “much more”;xi)Global rating of overall change in hip problem, scored on a 7-point Likert scale for “change in your hip problem since you began the study” from “much worse” to “much better” when compared to baseline.

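### The MCID responder model omits baseline pain, although response is defined by change from baseline; adding it is a free, minor gain in precision for a secondary outcome

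*Protocol article*

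**What the plan says.** Under Outcome measures, secondary outcome (v) is hip pain "measured as the proportion who meet or exceed the minimal clinical important difference (MCID) in NRS pain (at least 1.8 units of improvement"). Under Statistical analyses, this and the other binary outcomes are compared by risk differences and risk ratios "calculated from logistic regression models adjusted for the stratifying variables of site location and sex", fitted by generalised estimating equations to allow for clustering.

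For the primary continuous outcome, the same section says: "The model will be adjusted for baseline values and the stratifying variables of site (Sydney/Melbourne) and sex". Randomisation is stratified by site and sex only (Randomisation and allocation concealment). Eligibility requires average pain of at least 4 on the 0 to 10 scale (Participants).

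A full statistical analysis plan is promised before the formal analysis. The covariates of the binary model are nevertheless already stated here, so this is a choice made and not a detail left open.

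**The concern.** Responder status is baseline minus follow-up, cut at 1.8 units. Unless baseline and follow-up are very highly correlated, people who start with more pain tend to improve more, partly through regression to the mean, so baseline pain predicts response. Neither the stratification nor the responder model takes account of it.

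Two things follow. The risk difference is less precise than it could be with about 40 evaluable people per arm. And if one arm happens to start with more pain, its responder proportion rises for that reason alone. The primary mean difference, read beside it, has been corrected for that same imbalance, so the two results could diverge by chance.

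**Working it through.** **Inputs from Sample size calculation.** Target difference: "We aim to detect a MCID between groups of 1.8 NRS units in change in overall hip pain severity". Spread: "We have assumed a conservative standard deviation at baseline across all participants of 2.5 units". Correlation: "conservative correlation between baseline and 6-month scores of 0.25". Clustering: "an intra-cluster correlation of 0.05 and that there will be 5 dietitians treating approximately 8 patients each". Result: "we need 40 per arm to achieve 80% power to detect the MCID in pain at a 0.05 significance level".

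**The plan's own figure.** It concerns the primary outcome; no power is stated for responders.
- Baseline-adjusted SD: 2.5 × √(1 − 0.25²) = 2.42.
- Unclustered n per arm: 2 × (1.96 + 0.84)² × 2.42² / 1.8² ≈ 28.4.
- Design effect: 1 + (8 − 1) × 0.05 = 1.35. In both arms: 28.4 × 1.35 ≈ 38.3, so 39, close to 40. In the dietitian arm only: 28.4 × (1 + 1.35)/2 ≈ 33.4, so 34.
- Attrition: 40 / 0.8 = 50.

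The point here uses only the 40 evaluable per arm.

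**How strongly baseline predicts change.** For baseline SD s_B, follow-up SD s_F and correlation r:

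corr(baseline, improvement) = (s_B − r·s_F) / √(s_B² + s_F² − 2·r·s_B·s_F).

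With both SDs 2.5 and r = 0.25 this is √(0.75/2) = 0.61, and 0.61² ≈ 0.375 of the variance of change.

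The entry rule confines baseline to 4–10. Even a flat spread over those seven integers has SD √((7² − 1)/12) = 2.0, so 2.5 is unlikely among those enrolled. With s_F kept at 2.5 and r = 0.25, s_B = 1.73 gives (1.73 − 0.625)/2.66 = 0.42, and s_B = 1.36 gives (1.36 − 0.625)/2.53 = 0.29. The simulated values below, on a rounded and bounded scale, are 0.44 and 0.31.

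**Simulation.** 80 evaluable, 2,000 runs per scenario, true difference 1.8, assumed control improvement 1.0, no dietitian clustering. The standardised risk difference comes from a logistic model with site and sex, without and then with baseline pain. Shift is the movement of the risk difference, in percentage points, per 1-unit baseline imbalance.

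| Baseline | r | Corr. with change | SE without → with | Variance saving | Power | Shift without → with |
|---|---|---|---|---|---|---|
| Unrestricted, SD 2.5 | 0.25 | 0.61 | 0.110 → 0.099 | 20% | 55% → 65% | 8.8 → −0.4 |
| 4–10, SD 1.73 | 0.25 | 0.44 | 0.109 → 0.103 | 11% | 66% → 71% | 9.9 → 0.8 |
| 4–10, SD 1.36 | 0.25 | 0.31 | 0.110 → 0.107 | 5% | 71% → 73% | 8.7 → 1.0 |
| Unrestricted, SD 2.5 | 0.5 | 0.50 | 0.108 → 0.100 | 14% | 75% → 81% | 7.2 → −0.3 |
| 4–10, SD 1.73 | 0.5 | 0.25 | 0.108 → 0.106 | 3% | 82% → 83% | 5.1 → 0.5 |
| 4–10, SD 1.36 | 0.5 | 0.08 | 0.104 → 0.105 | −1% | 86% → 86% | 1.8 → 0.6 |

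With a true difference of 1.0 the savings are similar: 23%, 11%, 4%, 14%, 2% and −2%. Other runs with slightly different settings gave 20–24% unrestricted at r = 0.25; 17% unrestricted at r = 0.5; 13% restricted (SD about 1.8) at r = 0.25; 6–7% restricted (SD about 1.3) at r = 0.25; and 4% restricted (SD about 1.8) at r = 0.5.

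**Typical chance imbalance.** The SD of the between-arm difference in mean baseline pain is s_B × √(2/40): 2.5 × 0.224 = 0.56, 1.73 × 0.224 = 0.39, 1.36 × 0.224 = 0.30. Multiplied by the shift, a 1-SD imbalance moves the unadjusted risk difference by 8.8 × 0.56 ≈ 4.9 points in the first row, 5.1 × 0.39 ≈ 2.0 in the fifth and 1.8 × 0.30 ≈ 0.5 in the last.

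**The case against.** The case for leaving the model alone is a fair one. This is one of eleven listed secondary outcomes. Efficacy conclusions rest on 6-month change in the primary outcome, whose model already adjusts for baseline. Adjusting for the stratification factors is a recognised minimum, and one covariate set for all binary outcomes is simple. The protocol calls its correlation of 0.25 conservative, so the true value may be higher and the gain smaller. A typical imbalance moves the risk difference by 5 points or less, against a standard error of about 10 to 11. On an integer scale response means a 2-point drop, and everyone entering at 4 or more has room for that. The simulations also leave out dietitian clustering, so the exact gain under the planned estimating equations is not shown.

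All of this stands and limits the weight of the point. It does not give a reason to omit the covariate. Where baseline predicts change hardly at all, including it costs 1 to 2% in variance at most; elsewhere it helps.

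Two stronger readings are tempting. A reader might infer that the responder comparison is biased. It is not: randomisation makes it valid without baseline adjustment, and the simulated mean risk differences with and without baseline agree (0.231 and 0.232 in the first row). A reader might also take the 24% variance cut, or a rise in power from about 54% to 66%, as the expected loss. Those figures need a baseline SD of 2.5, which the entry rule makes implausible, and the protocol sets no power target for responders.

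**Conclusion.** The point holds as a free improvement of minor severity. The responder model leaves out a baseline measure that the primary model uses and that forms part of the responder definition.

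At 40 evaluable per arm, the variance of the risk difference would fall by roughly 0 to 14% (allowing for simulation error) if the entry rule narrows baseline pain. It would fall by at most about 20 to 24% if SD 2.5 and r = 0.25 held unrestricted. A correlation of 0.5 does not by itself remove the gain: with an unrestricted SD of 2.5 the saving is still about 14 to 17%, and it nears zero only when the baseline is also narrow.

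Adjustment removes a shift of about 4 to 10 points per unit of imbalance in most scenarios, falling to 1 to 2 points in the narrowest baseline at r = 0.5. That is typically about 1 to 5 points in one trial.

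The figures assume independent participants, a control improvement of 1.0 in the tabulated runs, and a follow-up SD of 2.5. The restricted baseline SDs are assumptions, since the protocol gives none for the enrolled population. The primary analysis is unaffected.

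**What to change.** In the statistical analysis plan, before any unblinded analysis, add baseline NRS pain as a continuous covariate to the responder logistic model at 6 and 12 months, alongside site and sex. Obtain the risk difference and risk ratio by standardising the predicted probabilities over the observed covariates. The estimates then keep their marginal meaning and only the precision changes. The handling of clustering by generalised estimating equations need not change. Binary outcomes without a baseline value can keep site and sex only.

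The cost is one extra term in the model statement. Baseline NRS pain is already collected from every participant, so no new data are needed and the sample size does not change.

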### Timelines

Ethical approval was obtained from the Human Research Ethics Committee of The University of Melbourne in March 2021. Recruitment commenced in May 2021 and will be completed in May 2022, pending COVID-related restrictions. The trial is due for completion in May 2023 when all participants will have completed 12-month data.

### Patient and public involvement

The trial has been endorsed by the Australia and New Zealand Musculoskeletal (ANZMUSC) Clinical Trial Network indicating its high priority and quality, importance to consumers/patients, clinicians and policy makers, and its potential to improve patient outcomes. The ANZMUSC endorsement process included an assessment of the protocol by a scientific and consumer advisory group that supported the design of the trial.

### Dissemination

Study findings will be disseminated through publication in peer-reviewed journals and conference presentations.

## Discussion

This protocol presented the rationale, theoretical foundation, and protocol for a two-arm comparative effectiveness clinical trial comparing diet and exercise to exercise only for people with hip OA. Clinical guidelines recommend weight loss for hip OA in the absence of robust evidence on the effectiveness of diet interventions for hip OA. High quality trials specific to hip OA have been highlighted by leading international organisations as a priority [5]. Findings from the ECHO trial will assist clinicians and patients with hip OA in determining whether a diet intervention in addition to exercise is beneficial for hip OA symptoms compared to exercise alone.

## Data Availability

The datasets used and/or analyses including statistical code will be available from the corresponding author ([contact]) on reasonable request once the study has been completed.

## Abbreviations

ANZMUSC: Australia & New Zealand Musculoskeletal Clinical Trials Network
ANCOVA: Analysis of Covariance
AQoL-6d: Assessment of Quality of Life instrument − 6 dimension
BMI: Body Mass Index
CHESM: Centre for Health, Exercise and Sports Medicine
CI: Confidence Interval
MCID: Minimal Clinically Important Difference
NRS: Numeric Rating Scale
OA: Osteoarthritis
OARSI: Osteoarthritis Research Society International
PLS: Plain Language Statement
RCT: Randomised Controlled Trial
SD: Standard Deviation
VLCD: Very Low-Calorie Diet
